### 4.1. IBS-SSS

The IBS-SSS, developed by Francis, Morris, and Whorwell, is a 5-item survey that focuses on:the severity of abdominal pain (IBS-SSS1),the frequency of abdominal pain over the last 10 days (IBS-SSS2),the severity of abdominal bloating (IBS-SSS3),dissatisfaction with bowel habits (IBS-SSS4),interference with quality of life over the past 10 days (IBS-SSS5) [32].

Subjects will respond to each question on a 100-point visual analog scale. Each of the five questions generates a maximum score of 100 points, and the total scores range from 0 to 500, with higher scores indicating more severe symptoms.

### 4.2. IBS-GIS

The IBS-GIS is a tool for assessing patient-rated changes in IBS symptom severity using a 7-point Likert scale, ranging from symptoms substantially worse (1 point) to substantially improved (7 points) [33]. Participants will be asked to answer the question “Have you felt any change in the severity of your symptoms over the past 7 days compared to how you felt before the medicine was taken?” The answers will be recorded based on a 7-point scale:1 point—“I feel that the symptoms have worsened significantly”;2 points—“I feel that the symptoms have moderately worsened”;3 points—“I feel that the symptoms have slightly worsened”;4 points—“I feel no change”;5 points—“I feel a slight improvement”;6 points—“I feel moderate improvement”;7 points—“I feel significant improvement”.

IBS-GIS scores of >4 indicate an improvement, scores of <4 indicate a worsening, and a score of 4 indicates no change in symptom severity.

### 4.3. IBS-AR

IBS-AR is a dichotomous single-item questionnaire that asks participants “Over the past week, have you had adequate relief of your IBS symptoms?” The answer can be YES or NO.

### 4.4. BSF Scale

The type of stools will be assessed using the BSF Scale that classifies feces into seven types: types 1–2 indicate constipation, types 3–4 are “normal” stools, and types 5–7 indicate diarrhea [31].

### 4.5. IBS-QOL

IBS-QOL is a 34-item measure assessing the degree to which IBS interferes with patient quality of life [34]. Each item is rated on a 5-point Likert scale, thus, yielding a total score theoretically ranging from 34 to 170 points, with higher scores indicating worse QOL.

### 4.6. Patient’s Diary

Participants will be asked to fill out a diary every day. The diary will contain information on the number of bowel movements per day, the type of stools, and the severity of the following symptoms: abdominal pain, bloating, fecal urgency, and feeling of incomplete evacuation. The type of stools will be assessed using the BFS scale. Specific IBS symptoms, except for the feeling of incomplete evacuation, will be assessed using a patient-rated 5-point Likert scale, with 0 points indicating no symptoms, and 1–4 points indicating various levels of symptom severity, with higher scores indicating worse symptoms. The feeling of incomplete evacuation will be assessed using a 2-point scale, with 0 points indicating no such feeling and 1 point indicating the feeling of incomplete evacuation.

### 4.7. Telephone Interview

Telephone interviewers will call participants once a week to monitor study preparation intake and daily diary entries, and to collect data on side effects and the use of other medications, particularly antibiotics. Adverse events will be evaluated on a scale from 0 (no) to 1 (yes). Participants who take antibiotics will be withdrawn from the study.

### 4.8. Study Endpoint Definition

The prospective defined primary efficacy outcome will be changes in IBS symptoms and quality of life measured with the use of the IBS-SSS, IBS-GIS, IBS-AR, and IBS-QOL questionnaires.

Secondary efficacy variables will include:the number and type of stools assessed with the BSF scale,pain, bloating/abdominal distension, stool urgency, feeling of incomplete evacuation after a bowel movement assessed with a patient-rated Likert scale,adverse events,anthropometric measurements and BMI,body composition,cytokine (IL-6, MIP-1ß) levels.

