## Abstract

Irritable bowel syndrome (IBS) is a functional gastrointestinal disease in the pathogenesis of which gut dysbiosis may play an important role. Thus, probiotics, prebiotics, or microbiota metabolites, such as butyric acid, are considered to be effective therapy for IBS. However, there are still no trials presenting the efficacy of these three biotic components administered simultaneously. This study aims to evaluate the effects of the product comprising sodium butyrate, probiotics, and short-chain fructooligosaccharides (scFOS) on the severity of clinical IBS symptoms and the quality of life (IBS-QOL). This is a randomized double-blind placebo-controlled trial conducted in 120 adults with IBS diagnosed according to Rome IV criteria. The intervention group (n = 60) will receive a mixture of the following components: 300 mg of colon-targeted microencapsulated sodium butyrate combined with probiotic *Lactobacillus* strains (*L. rhamnosus* and *L. acidophilus*) and *Bifidobacterium* strains (*B. longum*, *B. bifidum*, *B. lactis*), and 64 mg of prebiotic scFOS. The control group (n = 60) will receive a placebo (maltodextrin). The primary outcomes will be changes in IBS symptoms with the use of the IBS-Severity Scoring System (IBS-SSS), IBS-Global Improvement Scale (IBS-GIS), IBS-Adequate Relief (IBS-AR), and IBS-QOL after 12 weeks of intervention. The secondary outcomes will be the type of stools, patient-recorded symptoms, adverse events, anthropometric and nutritional parameters, and inflammatory cytokine levels. The findings will provide the first evidence of the use of a combination of three biotic compounds in IBS. The study was registered in the clinicaltrials.gov registry under the number NCT05013060.

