## 2. Experimental Design

### 2.1. Aim and Hypothesis

The main goal of the study is to assess the effects of the product comprising microencapsulated sodium butyrate and the probiotic mixture of two *Lactobacillus* strains (*L. rhamnosus* and *L. acidophilus*) and three *Bifidobacterium* strains (*B. longum*, *B. bifidum*, and *B. lactis*) and small amounts of prebiotic scFOS on the incidence and severity of clinical symptoms in patients diagnosed with IBS based on the Rome IV criteria. The primary hypothesis is that this mixture supplementation will reduce IBS symptoms and improve the patient’s quality of life.

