### 4.10. Statistical Analyses

#### 4.10.1. Sample Size Calculation

Based on the effects observed in the previous study, in which we used a similar probiotic and prebiotic combination, but without microencapsulated sodium butyrate, in IBS patients [27], we have estimated that a sample size of 35 participants per group would be required to reach clinical significance. With an estimated drop-out ratio of about 20%, the total sample size would need to be 80 participants, which would ensure 80% power to demonstrate significance with a *p*-value < 0.05. To further enhance the statistical power, the sample size was ultimately set to 60 participants/cases per group, with a total of 120 patients to be included in the study.

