#### 4.10.2. Statistics

The intergroup and intragroup differences in age, anthropometric parameters, and IBS symptom data across subsequent visits or weekly data from patient diaries or telephone interviews will be evaluated with two-sided paired or unpaired *t*-tests or repeated measures (RM) ANOVA after checking for equality of variances and normality of distribution using a Shapiro–Wilk test. If the data is not normally distributed, two-sample Wilcoxon paired or unpaired signed-rank tests will be used. Fisher’s exact test will be used for analyses of variables presented as percentages. The threshold of significance for all analyses will be set at α = 0.05.

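### Four unranked primary questionnaires share an unadjusted 0.05 with no rule for success; if a win on any one counts, the family-wise error is about 13% to 18.5%

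*Protocol article*

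**What the plan says.** - **Primary outcome.** Section 4.8 gives it as "changes in IBS symptoms and quality of life measured with the use of the IBS-SSS, IBS-GIS, IBS-AR, and IBS-QOL questionnaires". The Abstract uses the plural, opening with "The primary outcomes will be changes in IBS symptoms with the use of the IBS-Severity Scoring System (IBS-SSS" and closing its list with "IBS-Adequate Relief (IBS-AR), and IBS-QOL after 12 weeks of intervention". Neither place puts one questionnaire ahead of the others. Week 12 appears in the Abstract; 4.8 gives no time point.
- **Significance level.** Section 4.10.2 states: "The threshold of significance for all analyses will be set at α = 0.05". Comparisons of symptom data "will be evaluated with two-sided paired or unpaired" t-tests or repeated-measures ANOVA, with rank tests as the fallback and Fisher's exact test for percentages.
- **Hypothesis.** Section 2.1 reads "The primary hypothesis is that this mixture supplementation will reduce IBS symptoms and improve" quality of life. It joins two domains and does not tie them to the four scales.
- **Power.** Section 4.10.1 takes 35 per group from the effects seen in an earlier trial, allows for dropout, and gives a total "which would ensure 80% power to demonstrate significance" at p < 0.05. It then raises enrolment to 60 per group. It names no endpoint, effect size or standard deviation.

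**The concern.** A reader of the final report needs to know which pattern of results would have meant that the trial succeeded. With four equal primary scales, each judged at 0.05, the article allows at least two readings.

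- **Any one scale is enough.** A product with no effect then has four chances to produce a significant primary result, and the trial-level error is no longer 5%.
- **All four are needed.** The error is controlled, but the 80% power was derived for a single unnamed effect and says nothing about the chance of winning on all four.

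Without a rule, the scale that happens to come out best could be put forward after unblinding, and nothing in the article would mark that as a departure from plan.

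**Working it through.** **Inputs from the article.** Four primary scales (4.8); two-sided 0.05 for each (4.10.2); week 12 (Abstract); 35 evaluable per group for 80% power, about 20% dropout, 60 enrolled per group (4.10.1).

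**Assumptions, because the article gives no figure.** One between-group test per scale, and an equal correlation r between any two of the four test statistics, varied from 0 to 0.9.

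**1. The plan's own power figure.** The 35 per group cannot be reproduced, since no effect, standard deviation or endpoint is given. Solving backwards for a two-sample t-test with 35 per group, α = 0.05 and 80% power gives a standardised difference d = 0.68. This is used below as an implied value only.

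**2. Any one of four counts.** With independent tests:

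- Two-sided error = 1 − (1 − 0.05)^4 = 1 − 0.95^4 = 18.5%.
- Error in favour of the product = 1 − (1 − 0.025)^4 = 1 − 0.975^4 = 9.6%.

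The correlated cases come from simulating four equicorrelated normal statistics (2 million draws):

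| r | Any of four, two-sided | Multiple of 5% | Any of four, favouring product |
|---|---|---|---|
| 0 | 18.5% | 3.7 | 9.6% |
| 0.3 | 17.4% | 3.5 | 8.8% |
| 0.5 | 15.6% | 3.1 | 7.8% |
| 0.7 | 13.0% | 2.6 | 6.5% |
| 0.9 | 9.4% | 1.9 | 4.7% |

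The last column compares with 2.5% for a single test.

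**3. All four must be significant.** The type I error is at most 5%, so there is no inflation. For power, 20% dropout leaves 60 × 0.8 = 48 completers per group. At d = 0.68 each test then has 91% power. If that effect held on every scale:

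- r = 0: 0.909^4 = 68%
- r = 0.5: 76%
- r = 0.7: 80%

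If all 60 per group completed, the range for r = 0 to 0.7 would be 84% to 90%.

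**4. Cost of controlling the error.** For a continuous scale at d = 0.68:

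| Completers per group | Power at 0.05 | Power at 0.0125 (= 0.05/4) |
|---|---|---|
| 48 | 91% | 78% |
| 60 | 96% | 88% |

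A four-way Bonferroni split gives 1 − (1 − 0.0125)^4 = 4.9% if the tests are independent, and at most 5% under any correlation. Holm is never less powerful than this split. A fixed order keeps the first test at 0.05.

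**The case against.** **The inflation is conditional.** A reader might infer that the trial's false-positive risk simply is about three times 5%. The article does not support that. The multiple needs both an any-one-wins rule, which is nowhere stated, and moderate correlation, which is not given. The hypothesis joins symptoms and quality of life, which leans towards requiring both. The correlation could also be high: one IBS-SSS item already covers interference with quality of life, and IBS-GIS and IBS-AR are both global ratings over the past week. This stands, and it is why a range is given. The joint wording still settles nothing for the three symptom scales.

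**Direction.** The two-sided figures include results favouring placebo. For a wrong claim of benefit, the 6.5% to 9.6% column is the relevant one. This stands.

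**Visits.** One could count every primary scale at weeks 4, 8 and 12 and reach a much larger error. The Abstract ties the primary outcomes to 12 weeks, and section 4 lists the earlier visits only as measurement times. They are therefore not counted here.

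**Power of the all-four rule.** Multiplying the stated 80% gives 0.8^4 = 41%, which might suggest a badly underpowered trial. That 80% belongs to 35 per group, not to the 60 planned, so the 68% to 80% above is the relevant range. Even this, and the 78% at 0.0125, carries one back-solved effect over to all scales. IBS-AR is yes/no and IBS-GIS is a 7-point rating, so the figures need not hold for them.

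**Condensed article.** Multiplicity methods often sit in an analysis plan that is not shown, and 0.05 could be applied to adjusted p-values. Silence on the method would be no finding. But the article calls its primary outcome prospectively defined, gives four without rank, and sets one threshold for all analyses with no mention of adjustment. That is a stated rule, and an analysis plan that tested each scale at a stricter level would have to depart from it.

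**Conclusion.** The point holds in conditional form. The article fixes four equal primary scales and an unadjusted 0.05 for all analyses, and it does not say what counts as success.

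- If one significant scale at week 12 is enough, the two-sided family-wise error is about 13% to 18.5% for r from 0.7 to 0 (about 9% at r = 0.9). A false result in the product's favour has a chance of about 6.5% to 9.6%.
- If all four are needed, the error is controlled, but the stated 80% power is not the power of that test.

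On neither reading do the stated 5% and 80% both describe the primary claim. The correlations and the common effect size are assumptions. The missing success rule is not.

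**What to change.** Before unblinding:

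1. In 4.8, name one primary test at week 12. Total IBS-SSS, compared between groups, is a natural choice: section 5 reports it as significantly reduced in the earlier trial, which 4.10.1 uses for the sample size.
2. Test the other three scales at week 12 in a prespecified order at 0.05, stopping at the first non-significant result. The article supports no particular order among them, so the sponsor must choose and record one. Alternatively, use Holm across all four.
3. Amend 4.10.2 so that the unadjusted 0.05 does not apply to the primary family.
4. Label weeks 4 and 8, the secondary outcomes and the diary tests as exploratory.
5. State in 4.10.1 which test the 80% power refers to.

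This takes about a paragraph in the endpoint and statistics sections and a registry update, with no extra patients. With a fixed order, scales after the first failure lose confirmatory status. With Holm, the strictest step is at 0.0125, where power for a continuous scale is about 78% rather than 91% with 48 completers per group, if d = 0.68 applies.

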### 3.1. Inclusion Criteria

Patients with any of the following forms of IBS will be included:IBS-D—more than 25% of BSF type 6 and 7 stools, and less than 25% of type 1 and 2 stools;IBS-C—more than 25% of BSF type 1 and 2 stools, with less than 25% of type 6 and 7 stools;IBS-M—more than 25% of BSF type 6 and 7 stools and also more than 25% of type 1 and 2 stools.

To be eligible for the trial, subjects must meet all of the inclusion criteria and none of the exclusion criteria, as stated below.

The following inclusion criteria will be used:males and females aged from 18 to 70 years, inclusive;a good physical and mental condition assessed based on the patient’s history and physical examination;laboratory test results (complete blood count, blood chemistry panel) within normal limits or considered not to be clinically significant by the investigator;a voluntarily provided written informed consent;IBS with at least moderate symptom severity, defined as an IBS-Severity Scoring System (IBS-SSS) score of >175 points [32];the ability to strictly adhere to the investigators’ instructions regarding study procedures and protocol requirements.

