Changes in gut microbiota composition differ depending on the type of IBS [14]. In a study by Pozuelo et al., a lower abundance of butyric acid-producing bacteria was mainly observed in patients with IBS-D and IBS-M [15]. In contrast, El-Salhy et al. [37] found propionate and butyrate levels to be reduced in IBS-C patients, and butyrate levels to be increased in IBS-D patients in comparison with the control group. We plan to enroll patients with all three types of IBS (IBS-D, IBS-C, and IBS-M). Thus, the current study will allow us to determine in which type of IBS patients the study combination of butyrate sodium, probiotics, and small amounts of scFOS has the best effectiveness.

In our study, we have decided to administer the butyrate sodium + probiotics + scFOS preparation for 12 weeks, which allows us to expect an improvement in specific IBS symptoms measured with the use of international scales (IBS-SSS, IBS-GIS, IBS-AR) and patients’ QOL. As SCFAs (including butyric acid) have been estimated to provide about 10% of the total dietary energy supply in humans [38] and may also stimulate lipogenesis [39] we have planned to assess the impact of SCFA supplementation on body composition, anthropometric measurements, and BMI. We also suspect that a combination of sodium butyrate, probiotics, and small amounts of prebiotics will affect the inflammatory processes present in IBS patients, which we will be able to demonstrate by analyzing selected serological biomarkers (IL-6, MIP-1ß).

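### The secondary stool endpoint (number and BSF type) has no direction of benefit, yet IBS-D, IBS-C and IBS-M are enrolled together and the named tests carry no subtype term

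*Protocol article*

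**What the plan says.** - **Endpoint.** Section 4.8 puts "the number and type of stools assessed with the BSF scale" first among the secondary efficacy variables. It gives no direction of improvement, no measure of normalisation and no restriction to a subtype.
- **Scale.** Section 4.4 reads the BSF scale as follows: "types 1–2 indicate constipation, types 3–4 are “normal” stools, and types 5–7 indicate diarrhea".
- **Population.** Section 3.1 states "Patients with any of the following forms of IBS will be included". It defines IBS-D as "more than 25% of BSF type 6 and 7 stools, and less than 25% of type 1 and 2 stools" and IBS-C as "more than 25% of BSF type 1 and 2 stools, with less than 25% of type 6 and 7 stools". IBS-M has an excess at both ends.
- **Analysis.** Section 4.10.2 assigns visit data and weekly diary data to paired or unpaired t-tests, repeated measures ANOVA or Wilcoxon tests, and percentages to Fisher's exact test. It names no subtype factor or stratum.
- **Randomisation.** Section 2.3 specifies blocks of 4 and mentions no stratification by subtype.
- **Subtype intent.** Section 5 says the trial will show in which IBS type the product works best. Sections 4.8 and 4.10.2 contain no analysis that would do this.

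**The concern.** On this scale a lower type is better for a patient with loose stools and worse for a patient with hard stools. IBS-D and IBS-C are defined by the two ends, so an arm difference in raw type over all patients has no better side. Stool number has the same difficulty if benefit means fewer stools in IBS-D and more in IBS-C.

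Two things are at stake. A product that normalises stools in both subtypes may show little or nothing on this endpoint. And if a difference does appear, its sign cannot be read as benefit or harm. Leaving the measure open also allows a later choice among mean type, percentage normal and subtype results.

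**Working it through.** The protocol gives no figure for the stool endpoints, so there is none to reproduce.

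**Direction, from the protocol's own scale.** A move from type 6 to 4 in IBS-D is −2, and a move from type 2 to 4 in IBS-C is +2. In equal shares these average to 0, although every such patient has become normal.

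**Inputs for the size**
- From the protocol: 60 per arm, about 20% dropout, α = 0.05 (section 4.10.1 and 4.10.2). Completers: 60 × 0.8 = 48 per arm.
- Assumed, because the documents do not give them: control means 6 (D), 2 (C) and 4 (M); SD 1 within subtype; a true shift of 0.8 toward type 4 in D and C and none in M; the subtype mix, which is varied.

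**Pooled raw type.** Write D, C and M for the shares, and s for the displacement from type 4 (2 in control, 2 − 0.8 = 1.2 in treated).
- Arm difference = −0.8 × (D − C)
- Variance in an arm = 1 + (D + C)s² − [s(D − C)]²
- SE = √[(V_control + V_treated)/48]
- Two-sided power = Φ(|difference|/SE − 1.96) + Φ(−|difference|/SE − 1.96)

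Example, 60/20/20: difference = −0.8 × 0.4 = −0.32. V_control = 1 + 0.8 × 4 − 0.8² = 3.56. V_treated = 1 + 0.8 × 1.44 − 0.48² = 1.92. SE = √(5.48/48) = 0.338. Ratio 0.95, power 16%.

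**Distance from type 4.** The mean of |N(s, 1)| is 2.017 at s = 2, 1.312 at s = 1.2 and 0.798 at s = 0. The arm difference is therefore −(2.017 − 1.312)(D + C) = −0.705(D + C). The variance in an arm is (D + C)(s² + 1) + M − mean².

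| D/C/M | Raw difference | SE | Power, raw | Distance difference | SE | Power, distance |
|---|---|---|---|---|---|---|
| 40/40/20 | 0.00 | 0.364 | 5% | −0.56 | 0.191 | 84% |
| 40/30/30 | −0.08 | 0.346 | 6% | −0.49 | 0.190 | 74% |
| 50/25/25 | −0.20 | 0.346 | 9% | −0.53 | 0.191 | 79% |
| 60/20/20 | −0.32 | 0.338 | 16% | −0.56 | 0.191 | 84% |
| 70/10/20 | −0.48 | 0.303 | 36% | −0.56 | 0.191 | 84% |

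Simulation with t-tests agrees: 5%, 6%, 9%, 16% and 34% to 36% for raw type, and 73% to 84% for distance.

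**Change from baseline instead of follow-up value.** With SD of change 1, pooled power at the first four mixes is 5%, 6%, 15% and 29%. Removing the baseline spread helps, but the opposing signs remain.

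**Second check with another effect size.** The protocol's 35 per group at 80% power implies a standardised difference of (1.96 + 0.84) × √(2/35) = 0.67. That figure is not specific to stools. Apply 0.67 SD toward normal in D and C, none in M, at 60 per arm. Pooled power is 5% when D and C shares are equal, and 6%, 14%, 28% and 56% at 40/30/30, 50/25/25, 60/20/20 and 70/10/20. Scored toward normal by subtype, the same four mixes give 71%, 77%, 82% and 82%.

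**The case against.** **Pooling is not stated.** A reader might infer that the protocol prescribes an all-patient comparison. It does not say so; this follows only from the absence of any subtype term. Section 5 shows interest in subtypes, and an analysis plan that is not shown could split by them. That stands, and the point must be worded conditionally. It does not remove the point: the direction of benefit belongs to the endpoint definition, which section 4.8 does give.

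**A percentage of normal stools would fit the text.** Section 4.4 groups the types, section 4.10.2 allows for percentages, and a mean BSF score appears nowhere. This is fair, and it is the remedy proposed for stool type. But the protocol does not define the endpoint that way, and stool number has no such escape.

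**Cancellation is the extreme case.** A reader might infer that a true effect would always vanish. It does so only when the IBS-D and IBS-C shares and effects balance. Otherwise it is diluted, and with few IBS-C patients the loss is moderate.

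**False positives.** A reader might infer that a chance excess of one subtype in an arm makes spurious findings more likely. Under randomisation that imbalance is already part of the test's error rate. With no treatment effect and subtype drawn at random, the pooled t-test rejected 4.4% to 5.5% of the time across five mixes. The cost is power and interpretability, not type I error.

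**Fisher's test.** From "Fisher’s exact test will be used for analyses of variables presented as percentages" a reader might infer that individual stools would be counted as independent. Nothing in the protocol makes the stool the unit of analysis, and per-patient proportions exist for this test (IBS-AR yes/no, IBS-GIS improvement, adverse events scored 0 or 1).

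**Conclusion.** The point holds in conditional form. As written, the stool endpoint has no direction of benefit in a population drawn from both ends of the scale. An all-patient comparison of raw type or number would dilute a normalising effect and, in the balanced case, cancel it. In the main model the power for raw type is about 5% to 35% over the mixes tried, against 73% to 84% for a measure aligned with normal.

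These figures rest on the assumed mix, shift and SD and on a normal model for a bounded seven-point scale. They use distance from type 4 as a stand-in; power for the percentage of type 3–4 stools was not computed, and stool number was not simulated. The issue is confined to a secondary endpoint. The four primary instruments each run in one direction and are unaffected. It should be settled before unblinding.

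**What to change.** 1. Define the stool-type endpoint as each patient's percentage of diary stools of types 3–4, the range section 4.4 calls normal, with one value per patient per period.
2. Compare arms on this value with adjustment for the patient's run-in value and for IBS subtype. The 7-day diary kept before the product is started (section 2.2) supplies the run-in value.
3. Analyse raw BSF type and stool number within IBS-D and within IBS-C, with the direction of benefit stated for each. Label these descriptive: at a 40/30/30 mix and 48 completers per arm, IBS-C would have about 0.3 × 48 ≈ 14 patients per arm.

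The cost is analysis programming and lower precision within subtypes. The daily diary already collects the number and type of stools, so no new data are needed.
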